## Abstract

**Background:**

Despite increased investment in its recognition and treatment, depression remains a substantial health and economic burden worldwide. Current treatment strategies generally focus on biological and psychological pathways, largely neglecting the role of lifestyle. There is emerging evidence to suggest that diet and nutrition play an important role in the risk, and the genesis, of depression. However, there are limited data regarding the therapeutic impact of dietary changes on existing mental illness. Using a randomised controlled trial design, we aim to investigate the efficacy and cost-efficacy of a dietary program for the treatment of Major Depressive Episodes (MDE).

**Methods/Design:**

One hundred and seventy six eligible participants suffering from current MDE are being randomised into a dietary intervention group or a social support group. Depression status is assessed using the Montgomery–Åsberg Depression Rating Scale (MADRS) and Structured Clinical Interview for Diagnostic and Statistical Manual of Mental Disorders (Non Patient Edition) (SCID-I/NP). The intervention consists of 7 individual nutrition consulting sessions (of approximately 60 minutes), delivered by an Accredited Practising Dietitian (APD). Sessions commence within one week of baseline assessment. The intervention focuses on advocating a healthy diet based on the Australian Dietary Guidelines and the Dietary Guidelines for Adults in Greece. The control condition comprises a befriending protocol using the same visit schedule and length as the diet intervention. The study is being conducted at two locations in Victoria, Australia (a metropolitan and regional centre). Data collection occurs at baseline (pre-intervention), 3-months (post-intervention) and 6– months. The primary endpoint is MADRS scores at 3 months. A cost consequences analysis will determine the economic value of the intervention.

**Discussion:**

If efficacious, this program could provide an alternative or adjunct treatment strategy for the management of this highly prevalent mental disorder; the benefits of which could extend to the management of common co-morbidities including cardiovascular disease (CVD), obesity, and type 2 diabetes.

**Trial registration:**

NCT01523561

## Background

Depression is currently a leading cause of health and economic burden, internationally
[1]. Increased investment in recognition and treatment has failed to improve depression outcomes substantially in recent years, suggesting that other factors may be influencing the burden of this condition
[2]. Traditionally, treatment of depression has primarily focused on targeting biological and psychological pathways
[3,4]. Accumulating evidence now suggests that lifestyle factors such as diet quality contribute to a number of mental illnesses
[5] and play an important role in the risk and genesis of depression specifically
[6]. Dietary modification is widely recognised and promoted for the primary prevention of non-communicable disorders, such as cardiovascular disease (CVD), obesity and diabetes, yet has not been considered for the management of mental illness. To date, there are virtually no data regarding the therapeutic impact of dietary changes on depression.

This impact of habitual diet on the common mental disorders, is garnering significant scientific and public interest worldwide. There are many published studies providing consistent support for an association between habitual diet quality and depression
[7-12]. For example, in a population based sample of 1046 Australian women aged 20–94 years, a ‘healthy’ dietary pattern was associated with a reduced likelihood of clinically diagnosed depressive disorders, whereas a dietary pattern comprising processed and ‘unhealthy’ foods was associated with an increased likelihood of psychological symptoms and depression
[7]. Higher diet quality scores were also associated with reduced psychological symptoms
[7]. The associations between diet quality and mental illness have also been shown in the Hordaland Health Study of 5731 adults in Norway where participants with better quality diets were less likely to be depressed or anxious
[8]. This association was further investigated in a cross sectional study of more than 7000 Australian adolescents that found dose–response relationships between two measures of diet quality: healthy (negative) and unhealthy (positive) and the likelihood of adolescent depression, after adjustment for confounders
[9]. A population based study has also demonstrated a cross sectional and longitudinal relationship between diet quality and mental health in approximately 3000 Australian adolescents
[10]. Importantly, improvements in diet quality were mirrored by improvements in mental health, while reductions in diet quality were associated with declining psychological functioning over the two year follow up period
[10].

Similarly, recent prospective data from the SUN Cohort study in Spain demonstrated an inverse association between the level of adherence to a Mediterranean dietary pattern and the risk for incident depression in more than 10,000 adults
[11]. The Whitehall II cohort study of 3486 participants found an increased risk of self-reported depression after five years for those adhering more strongly to a ‘western’ style diet pattern, and a reduced risk for those following a ‘whole foods’ diet pattern
[12]. Interestingly, these studies have identified that when ‘unhealthy’ dietary patterns were assessed in relation to depression, they showed positive associations with depression
[7,9,10,12], indicating that what is excluded from the diet may be as important as what is included.

These recent data consistently support a role for diet quality in depressive illness
[7-12]. However, there are currently no available data regarding the therapeutic impact of dietary changes on existing mental illness. Studies involving dietary interventions, in non-psychiatric conditions, have demonstrated that diet can be successfully modified, leading to physiological changes that have implications for improved mental health
[13,14]. Taken together with previous data indicating success with individualised nutrition education counselling in those with mental illness
[15,16], an intervention targeting dietary improvement may also be feasible for individuals with depression. If found efficacious, such a treatment strategy has the advantage of being of population wide public health importance, and of substantial additional benefit across many disease states
[6].

This paper presents the study protocol for the SMILES trial: “Supporting the Modification of lifestyle In Lowered Emotional States.” This is a randomised controlled trial that aims to investigate the efficacy and cost-efficacy of dietary improvement in the treatment of Major Depressive Episodes (MDE). We hypothesise that a structured dietary intervention, focusing on dietary improvement, will be superior to a control condition (befriending) in the treatment of MDE.

## Methods

### Study design

This is a 12-week, parallel group, single blind, randomised, controlled trial of a dietary intervention for the treatment of moderate to severe depression. We are currently enrolling 176 participants over two sites; Barwon Health in Geelong and St. Vincent’s Health in Melbourne (Victoria, Australia). Recruitment and intervention are anticipated to occur over a 1.5-2 year period. Participants are randomised to receive either the dietary intervention or a control condition (social support). Participants in both groups complete assessments prior to program commencement (baseline), at program completion (3-months) and at a 6-month follow-up (via telephone).

### Study aims

We aim to investigate the efficacy of dietary improvement in the treatment of MDE. The primary outcome includes changes in MDE using the Montgomery-Åsberg Depression Rating Scale (MADRS). Secondary outcomes include; depressive and anxiety symptoms, functioning, quality of life, and changes in targeted dietary behaviours, cardiovascular and metabolic risk. A secondary aim is to evaluate the cost efficacy of the intervention from a societal perspective at 3 months.

### Participant eligibility

#### Inclusion criteria

Eligibility criteria includes participants who are: aged 18 or over and can provide informed consent; successfully fulfill the Diagnostic and Statistical Manual of Mental Disorders 4 (DSM-IV-TR) diagnostic criteria for Major Depressive Disorder, Single Episode or Recurrent, score 18 or over on the MADRS
[17] and score 68 or less in a Dietary Screening Tool (DST)
[18], modified for Australian diets, during screening. If participants are on antidepressant therapy, they are required to be on the same treatment for at least two weeks prior to randomisation. Participants must be readily available for a 3-month period and have the ability to eat foods as prescribed, without religious, medical, socio-cultural or political factors precluding participation or adherence to the diet.

#### Exclusion criteria

Participants are ineligible if they have: a concurrent diagnosis of bipolar I or II disorder; two or more failed trials of antidepressant therapy for the current MDE; known or suspected clinically unstable systemic medical disorder; pregnancy; commencement of new psychotherapy or pharmacotherapy within the preceding fortnight; severe food allergies, intolerances or aversions; current participation in an intervention targeting diet or exercise; a primary clinical diagnosis of a personality disorder; or a current substance use disorder.

### Sample recruitment

Community based recruitment strategies are used to recruit study participants. These include advertisements in local newspapers and radio stations; flyers in medical waiting rooms, pharmacies and university campuses; newsletters; and contact with potential referral sources, for example, general practitioners, private psychiatrists and local psychiatric inpatient units. Social media, such as Twitter and Facebook, is also used as a means of recruitment.

Prospective participants express their interest to the Clinical Trial Co-ordinator (CTC) through email or a phone call. Trained Research Assistants (RA) assess initial eligibility using a specifically developed telephone screening tool. If the individual meets these preliminary inclusion criteria, they are invited to attend a face-to-face screening session to determine full eligibility.

### Study procedure

#### Screening assessment

Prospective participants complete the DST
[18] to confirm “poor” dietary quality before enrolment. In order to adequately test the hypothesis that improving diet quality will reduce depressive symptomatology, those who have limited scope for improving their diet (DST scores ≥69) are excluded. If their score meets eligibility, the MADRS is administered to determine current depression severity. Depression status is subsequently confirmed using a psychiatric diagnostic interview (Structured Clinical Interview for DSM-IV, Non-patient Edition; SCID-I/NP). The Standardised Assessment of Personality – Abbreviated Scale (SAPAS)
[19] is used to screen for personality disorder. Once deemed to be eligible, participants complete a 7 day food diary and a food frequency questionnaire (FFQ) in the week leading up to baseline assessment. Participants attend a local (nominated) pathology clinic to provide fasting blood samples, before undertaking baseline assessment and randomisation (using a computer generated randomisation table) to either study condition.

### Study conditions

#### Diet intervention group

The intervention is a Modified Mediterranean diet, based on the Australian Dietary guidelines
[20] and the Dietary Guidelines for Adults in Greece
[21]. The diet is rich in vegetables, fruit and whole grains with an emphasis on increased consumption of oily fish, olive oil, legumes and raw unsalted nuts. Moderate consumption of lean read meat and reduced fat dairy is included. The diet comprises the following energy ratios: 39% total fat (e.g. 22% monounsaturated fat), 37% carbohydrates, 17% protein. In order to tailor the diet to a mental health population, the diet was designed to be manageable, sustainable and easy to follow. The primary focus is on increasing diet quality while reducing intake of energy dense, nutrient poor foods.

Participants receive seven individual sessions of approximately 60 minutes each, delivered by an APD. The first four sessions occur weekly and the remaining three sessions occur fortnightly. At the first session the dietitian conducts a diet history (incorporating a check list of commonly consumed foods) to assess usual dietary intake. Food models and metric measuring utensils are used to assist with the estimation of portion sizes.

Participants are provided with supporting written information specifically designed for the intervention to assist with achieving dietary adherence. These resources include healthy eating guidelines, convenient meal ideas, shopping lists, meal plans and recipe ideas. To encourage dietary adherence (and display the variety of foods that form the diet), participants are provided with a food hamper, incorporating the main components of the Modified Mediterranean diet. Recipes and meal plans using foods in the hamper are also available.

Additional sessions may incorporate label reading, food security (access to healthy food), motivational interviewing techniques and mindful eating as part of the individualised dietetic service. Participants are encouraged to set personalised goals at each session and identify barriers/motivators to change. At the final session, goals achieved are summarized with longer term strategies for achieving sustainable change discussed. The hamper is also provided at this session to promote longer term adherence.

#### Social support group

The control condition comprises a befriending protocol
[22], using the same visit schedule and length as the diet intervention. Befriending consists of a trained personal talking about neutral topics of interest to the participant with the intention of keeping the participant engaged and positive. The befriending condition
[22] aims to control for four factors: time, client expectancy, therapeutic alliance, and therapist factors when comparing to the intervention group in a RCT. This is done without engaging in techniques specifically used in the major models of psychotherapy. It is often used as a controlled condition for clinical trials of psychotherapy
[22]. Befriending is a highly effective validated controlled condition due to the simplicity of the program, and evidently appropriate to participants suffering from mental illness
[22].

In the penultimate session, both the dietitian and befriender provide each participant; pathology kits, 7-day Food Diary, Cancer Council of Victoria FFQ (CCVFFQ)
[23] and International Physical Activity Questionnaire (IPAQ)
[24] to be completed prior to the final session. Participants in the control group are provided movie tickets as compensation for their time and participation in the study.

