Dietary intake is assessed for each participant at baseline and post intervention to evaluate intake relative to the Australian Dietary Guidelines. Detailed information on foods and fluids consumed are collected using 7-day food diaries at the beginning and end of the intervention (1–7 days preceding the first session and 1–7 days preceding the final session) to monitor adherence to the intervention. These dietary assessments are also administered to the control group to capture any dietary changes made while being involved in the study.

RAs conducting data collection are blinded to participants’ group allocation. Prior to each assessment, participants are reminded not to reveal the group to which they have been assigned.

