### Data analyses

Data analysis will be conducted by a researcher blinded to the treatment conditions. A one-tailed analysis will be used to detect differences in MADRS scores between the intervention and control groups. Analyses will explore dose–response effects associated with intervention diet adherence. The primary efficacy analysis will assess average treatment group differences for the primary outcome measure (MADRS) over the entire study period and use a likelihood based mixed-effects model, repeated measures (MMRM) approach at each time point. Analysis of covariance (ANCOVA) will be used to compare differences between treatment means in changes from baseline to follow up. Intention to treat analysis will be employed. To assess confounding, covariates will include age, gender, Body Mass Index (BMI) physical activity levels, smoking and alcohol consumption. Non-parametric statistics will be used when assumptions for parametric methods are violated. Effect sizes will be calculated using Cohen’s guidelines. All tests of treatment effects will be conducted using an alpha level of 0.05 and reporting 95% confidence intervals. Multiple imputation will be employed for the management of missing data.

The economic evaluation will compare the dietary intervention to its comparator (the befriending group) in terms of both the costs and consequences as assessed by an incremental cost-effectiveness ratio (ICER). The primary study design is that of a cost consequence analysis (CCA)
[33].

Standard Australian unit costs (i.e. Medicare Benefits Schedule) will be applied to the resource use units collected. Costs will be presented in total and disaggregate forms such as those falling upon the health sector, patients, government and other sectors. The technique of ‘bootstrapping’ will be used to obtain confidence intervals for cost effectiveness ratios, since parametric techniques are inappropriate for use on skewed variables and ratios. The sensitivity of the results will also be tested against the variation in the utility weights and unit cost prices.

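### The 3-month pathology kit, food diary, FFQ and IPAQ are issued at a late treatment session, so missing diet, blood and activity data will track adherence to the randomised treatment

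*Protocol article*

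**What the plan says.** The hand-out of the follow-up materials is described under Social support group, for both arms: "In the penultimate session, both the dietitian and befriender provide each participant; pathology kits, 7-day Food Diary". The same sentence adds the FFQ and the IPAQ and sets the deadline: "to be completed prior to the final session". There are seven sessions, spaced as follows under Diet intervention group: "The first four sessions occur weekly and the remaining three sessions occur fortnightly". The control arm uses the same schedule.

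The Data collection and outcome measures section places the food diaries at "1–7 days preceding the first session and 1–7 days preceding the final session" and gives monitoring of adherence as their purpose. For habitual diet it refers the reader back to the earlier description. It also states, without any attendance condition, "Dietary intake is assessed for each participant at baseline and post intervention". Table 1 lists the FFQ, the IPAQ and the blood measures at baseline and 3 months.

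Study aims names targeted dietary behaviours and cardiovascular and metabolic risk among the secondary outcomes. Data analyses states "Intention to treat analysis will be employed", plans multiple imputation for missing data, and plans to explore dose-response with adherence to the intervention diet.

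**The concern.** Under intention to treat, outcomes should be sought from everyone randomised, whether or not they continue with treatment. Here the materials for four follow-up measurements pass through the therapist at a particular treatment session. A participant who stops after session 3 has no penultimate session at which to receive the pack and no final session from which to count the diary window. Whether the outcome is observed then depends on something that happens after randomisation and is part of the treatment.

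Two analyses are exposed. The first is the between-arm comparison of diet, lipids, glucose, fatty acids, carotenoids and physical activity. People may leave diet counselling and befriending for different reasons, so those still observed in the two arms need not be comparable. The second is the adherence analysis. The diary is the stated tool for monitoring adherence, and the people most likely to have adhered poorly are those for whom no follow-up diary would exist.

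**Working it through.** The documents give no figure on this point, so there is nothing to reproduce. The check sets the texts side by side and then gives an illustration on stated assumptions.

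**Step 1. Is there another described route at 3 months?**

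- Social support group: pack given by the dietitian or befriender at the penultimate session.
- Data collection and outcome measures: diary window tied to the final session; for habitual diet, a reference back to the earlier text, which for follow-up is the session hand-out.
- Table 1: time points only, no route.
- Screening assessment: before randomisation, the diary and FFQ are completed in the week before baseline and blood is given at a local pathology clinic. This shows that collection outside treatment sessions is feasible, but it is described for baseline only.

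So one route is described for follow-up, and nothing is said about participants who have stopped attending.

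**Step 2. How long must a participant stay to receive the pack?** Sessions 1 to 4 are weekly (three gaps of 1 week). Assuming the gap before session 5 is already a fortnight, session 6 falls 3 × 1 + 2 × 2 = 7 weeks after session 1. Someone who attends session 6 but misses session 7 still receives the pack, so the condition is reaching session 6, not completing all seven.

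**Step 3. Which measures are affected?**

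- On the hand-out list: pathology kit (lipids, glucose, fatty acids, carotenoids), 7-day diary, FFQ, IPAQ.
- Not on it: MADRS (clinician administered), HADS, POMS, AQoL-8D, weight, waist, blood pressure, and the DST at 6 months by telephone.

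**Step 4. What does multiple imputation do?** It keeps all randomised participants in the analysis. Under missing at random, values for people who left before session 6 are predicted from relations seen in people who stayed. With almost no observed follow-up among early leavers, the data hold little information on whether that prediction is right for them.

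**Step 5. Illustration of size.** Assumptions, none taken from the documents: a share m of the diet arm stops early, has no dietary change and is unmeasured; those who stay have mean change δ; the control mean change is about zero.

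- Effect over all randomised: (1 - m) × δ + m × 0 = (1 - m)δ.
- Effect from attenders, or from imputation that gives leavers the attenders' mean: δ.
- Inflation: δ / [(1 - m)δ] = 1/(1 - m).

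| m | Inflation | Observed per arm, from 88, if the same share is unmeasured in both arms |
|---|---|---|
| 5% | 1/0.95 = 1.05 | 88 × 0.95 = 83.6 |
| 10% | 1/0.90 = 1.11 | 88 × 0.90 = 79.2 |
| 15% | 1/0.85 = 1.18 | 88 × 0.85 = 74.8 |

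**The case against.** The strongest reply is that the article describes the routine case. It does not say that the session hand-out is the sole route or that people who miss it are not approached. Other statements are unconditional: dietary intake and self-report measures are to be obtained from each participant, and Table 1 attaches no attendance condition. A journal article may leave the chasing of non-attenders to the full protocol. This stands as far as it goes. A reader might infer that people who stop sessions are never asked for these data, and the document does not support that. It does not remove the point, because the described route and the diary window are both positively defined by late sessions, and the sections that say each participant supply no alternative.

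A reader might also infer that these outcomes become a completers-only analysis. That does not follow either: intention to treat with multiple imputation is stated, the imputation model is left open, and it could use sessions attended, baseline diet and other 3-month measures. The 6-month DST, taken by telephone independently of sessions, could help for diet quality. It is, however, a different instrument three months later and carries no direct information on blood markers or activity.

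Finally, it is tempting to size the loss from the Sample size section as 0.15 × 176 = 26 participants. That 15% is attrition over 6 months, not a rate of stopping sessions, and people lost to the study altogether would lack these data however the packs were issued. Nor can the 70 evaluable per group be used: 88 × 0.85 = 74.8, so that figure does not follow from 15%, which is a separate matter.

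**Conclusion.** The point holds as a weakness in how follow-up is fixed. The one described 3-month route for the pathology kit, diary, FFQ and IPAQ depends on reaching session 6. If it is followed as written, missingness in these measures will track adherence and may differ by arm. An analysis plan can model that, but it cannot recover data that were not collected.

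The consequence is confined to the diet and blood-marker secondary outcomes, physical activity and the adherence dose-response analysis. A reader might extend it to the primary endpoint. The documents do not support that, since the MADRS, like the HADS, AQoL-8D and anthropometry, is not among the items handed out.

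No size can be derived from the documents. The inflation of 1.05 to 1.18 for m from 5% to 15% rests on the assumptions of no change among early leavers, no measurement of them, a control mean change near zero, and an estimate based on attenders. The correction is worth making because it is cheap.

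**What to change.** Anchor both the issue of the pack and the diary window to a fixed time from randomisation instead of to the penultimate and final sessions. Have the trial co-ordinator, or another staff member who does not assess outcomes, send the kit, diary, FFQ and IPAQ to every randomised participant at that time, whether or not sessions are still attended. Using someone who is not an assessor protects the blinding of the research assistants. State in the protocol that stopping sessions is not withdrawal from assessment.

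The cost is postage and a change of wording. The instruments and laboratory arrangements already exist, and a local pathology clinic is already used at baseline. Some packs will not be returned, so missing data will be reduced, not removed.
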